## Abstract

**Aims/Background:**

The mental health challenges faced by frontline healthcare workers responding to emergencies have become a prominent public concern. Despite the consensus that Psychological First Aid (PFA) training can effectively support public mental health during emergencies through reducing acute distress and improving self-efficacy, yet it is concerning that previous flexible delivery and neglect for evaluating PFA training has resulted in unintended potential harms which may prevent further proactive uptake of this mental health prevention strategies. Establishing the feasibility of the PFA training through adapting to the local culture, tailoring to frontline healthcare context, and evaluating systematically may be helpful to inform a large trial, or ensure effective and sustained training delivery. This study aims to present a protocol for evaluating the feasibility and acceptability of a well-adapted PFA training intervention (Preparing Me) to address the implementation gap in this mental health promotion approach.

**Method:**

This is a two-armed feasibility randomized controlled trial (RCT) to be conducted among 80 Chinese frontline healthcare workers without prior related mental health training. Participants from the intervention group will receive an adapted PFA training program tailored to the Chinese frontline context to improve their knowledge and skills to support people in crisis. The primary objectives are to evaluate the training intervention's feasibility and the target population's acceptance of this educational intervention. The secondary objective is to obtain preliminary estimates of variability in participants' outcomes over a 3-months period. Measurements are taken pre-intervention (T0), post-intervention (T1), and at 1- and 3-months follow-up (T2–T3). A process evaluation using qualitative research with a subgroup of trainees, their clinical managers as well as trainers will be conducted to gain a comprehensive understanding of the intervention's acceptability and feasibility.

**Discussion:**

This present study protocol will help to establish whether this adapted PFA training intervention is feasible and accepted by the frontline healthcare workers, in preparation for a later effectiveness trial. It is anticipated that the resulted information would be an impetus to maximize usability and acceptance of this low-intensity PFA skillset by a wider population, thus supporting the mental health of frontline healthcare workers in dealing with crises for future emergencies.

**Trial Registration:**

This trial has been approved by the Institution Review Board from Central South University (LYG2020029) and by the Psychiatry, Nursing and Midwifery Research Ethics Committee at King's College London, England (LRS/DP-21/22-23161). It also has been processing registration at the Chinese Clinical Trial Registry.

## Introduction

The mental health challenges faced by healthcare workers is a major public health concern threatening health and economic prosperity of leading economies (1, 2). Working in crisis healthcare environments, healthcare workers providing direct services to patients have been experiencing increased patient volume and mounting demands, against a backdrop of limited resources; factors which are significantly associated with increased psychological stress (3, 4). This can in turn lead to burnout (BO), depression, anxiety disorders, sleeping disorders, and other mental illness (5). Health services' responding to the COVID-19 pandemic has been further exacerbated by these issues among frontline healthcare workers across the globe, which can, in turn, have a negative impact on health systems through decreased professionalism, and reduced care delivery and efficiency (6, 7).

The adverse mental health impact of public health crises on healthcare workers is not a new concern and is considered by some as a consequence of an historical underinvestment in mental health prevention for healthcare workers (8). There are two main issues here. Firstly, providing early psychological support to acutely distressed individuals has been well-recognized as critical to prevent the onset of mental illness, but the availability of early support is limited by insufficient onsite mental health professionals, limited resources, and insufficient recognition of the value of prompt psychological support for patients by frontline health workers themselves (7, 9). Secondly, apart from their pivotal role of caring patients, healthcare workers are at high-risk themselves arising from overwhelming stressful situations. Many are trained to prioritize physical problems rather than their own psychological needs—putting patients first; and acting as “heroes” whilst being conscious of the stigma associated with seeking emotional help for their own mental health distress (10, 11). The importance of individual healthcare workers recognizing and managing their own stress seems to be neglected.

Prior evidence has reported on short-term “mood boosters” to support the frontline workforce such as free-lunch, clapping for heroes, or practice telemedicine mindfulness (12, 13). Although these may offer temporary relief, they are no substitute for interventions to address the serious challenges frontline workers face regarding protecting their mental health and well-being. Some further argue that Self-Help Plus and stress management approaches may be ideal for stress and BO reduction (14), yet those appears to be insufficient of empowering them to address patients' need. Thus, investing in and accelerating preventive measures to reduce the workload burden on the healthcare workforce and practice self-care on a more permanent basis is imperative in the long term.

A recent scoping review of the impact of the COVID-19 pandemic on the physical and mental health of healthcare workers highlights the importance of fostering their resilience through proactive optimal provision of education, resilience training, and interventions to increase the confidence of staff in their preparedness to manage health care emergencies (7). Psychological First Aid (PFA) is one such intervention which has potential to deliver these benefits for healthcare staff capable of providing the necessary psychological support and practicing self-care. However, substantial challenges exist in its implementation may prevent its potential of this so-called cost-effective mental health promotion strategy.

### The Role of PFA to Support Public Mental Health During Emergencies

Psychological First Aid is an intervention to mitigate acute stress and foster resilience for crisis-affected victims which is promoted by public health authorities. Originally developed as a “do no harm” intervention to ensure the psychological recovery of people who have experienced traumatic stress in aftermath of the disaster (15, 16), PFA is effective to: (A) recognize their vulnerability (e.g., risk for crisis harm) and develop safety plans; (B) calm those who are emotionally distressed by the crisis; (C) improve disaster victims' self-efficacy to meet their emotional and practical needs; (D) support connectiveness and hope to protect individual well-being; and (E) facilitate access to more intensive assessment and intervention when indicated (16, 17).

Psychological First Aid as an early response intervention on reducing acute distress has several potential advantages. First, unlike traditional psychiatric interventions, PFA does not pathologize acutely distressed people; rather, it normalizes distress reactions and improves the coping abilities of traumatized disaster victims. This potentially reduce the stigma of being problematic in coping with crisis (18). Second, PFA does not involve psychiatric diagnosis; rather it involves approaching people in crisis, active listening, and providing practical assistance if needed via problem-solving, meeting basic needs or referring to professional care (19). Thus, it increases the scalability by training “lay people” to address the shortage of mental health professionals in frontline and reduce the stigma of seeking emotional help among acutely distressed individuals.

With the public emergencies increasingly prevailing across the globe and the emphasis of early psychosocial support in emergencies, PFA training has been widely applied as a first-line capacity-building approach to equip frontline workers within emergency response setting. A few studies conducted with frontline workers in humanitarian, disaster relief, and primary health sectors, have found that training in PFA has positively improved workers' knowledge of appropriate psychosocial responses and skills to support people in crisis situations, and enhanced their resilience to address adversity (20–23). Meanwhile, during the COVID-19 pandemic response, several institutions have started peer support programs of training in PFA for the support of healthcare workers. These reported anecdotal experiences suggest that it is a useful in-person, on-site support programme to foster resilience and self-efficacy (24–26).

The accessibility and utilization of PFA training to prepare especially the healthcare staff to ensure frontline psychosocial response is demanding, yet barriers to extend or proactively uptake PFA training to a wider group are substantial. First, the focus of PFA training on staff working exclusively in disaster settings which may lead to a misconception of PFA as a specific disaster response tool with less applications across non-disaster contexts and populations (27, 28). Second, most PFA training delivery is still the result of disaster-caused emergencies plans which result in just-in-time training. Current training delivery highlights the shortcomings of PFA training including inadequate guidance on adaptation, little motivation to evaluate, unclear training outcomes, and a lack of clarity about the core components of PFA training to ensure high fidelity (29). This is concerning that the previous flexible delivery with little motivation for evaluating PFA training has resulted in unintended potential harm to disaster victims, such as making false promises and confusion about role boundaries (30). Even worse, given the availability of evidence from training implementation science could further influence the therapeutic effect of the PFA intervention. Third, studies on the mechanisms through which PFA skills work to deliver patient benefit is still lacking, that may become the inhibitor to proactive scaling-up of training initiatives; for instance, few studies have investigated the longitudinal impact of PFA educational and implementation outcomes (e.g., trainees' adherence, preparedness, skills in real-world, well-being benefits).

Scholars suggest that PFA training should be accessible as rudimentary skill to increase frontline health care workers' coping ability, reduce their risk of distress and provide them with skills to deliver person-centered care (31). However, before establishing what extend potential benefits of PFA training can be contributed to the healthcare context, it seems to be neglected to determine the feasibility of the PFA training through adapting to the local culture, tailoring to frontline healthcare context, and evaluating systematically. Considering the COVID-19 pandemic is likely accelerate the uptake of PFA training, it is far more urgent to prioritize a well-adapted PFA training intervention thereby to effectively inform a randomized controlled trial (RCT) in a larger sample.

### “Preparing Me” Program—Support the Mental Health of Frontline Healthcare Workforce

In China, an inadequate investment to safeguard the mental health and well-being of the healthcare workforce has been well-documented during the COVID-19 pandemic response (32). Chinese healthcare workers have been increasingly required to respond to mental health crises arising from the growing psychosocial support needs of an enormous population, increased incidence of public health emergencies, insufficient, and unevenly distributed mental health resources, poor mental health literacy, and severe stigma toward help-seeking (33–35). The prior study has reported a remaining underdeveloped crisis mental health preparedness of healthcare workers and little attention is paid to capacity building through mental health training in China (36, 37). As highlighted by the COVID-19, it is far more imperative to establish evidence of a frontline capacity building approach to empower Chinese healthcare workers with the ability of recognizing and responding to psychological distress. Thus, this “Preparing Me” project (hereafter referred to as Preparing Me for frontline) comes at the opportune time which aims to adapt, tailor, and evaluate PFA training to frontline healthcare workers in China for use.

Among the three most influential PFA models, each with different priorities are the World Health Organization PFA guide (Psychological First Aid: Guide for Field Workers) (38), the National Child Traumatic Stress Network PFA guide (Psychological First Aid: Field Operations Guide) (39), RAPID model (The Johns Hopkins Guide to Psychological First Aid) (19). Of these, the present study involves adapting the John Hopkins Guide to Psychological First Aid for implementation and evaluation in China. The John Hopkins Model has been selected, over the other two models, because: (A) a small therapeutic RAPID PFA effect of reducing acute stress has been established in two RCTs among individual and group samples (40, 41); (B) its structured stepwise model aligns with empirical validation regarding its knowledge, skills, and attitudes (KSA) format for PFA competency statements so providing a foundation to quantitatively evaluate acquisition of the learning objectives (42); (C) the findings from John Hopkins' PFA capacity-building initiatives reveal a potential value of proactive preparedness to equip their public health workforce with PFA competencies representing 14 preparedness and emergency response centers (43–45). Given its emphasis on meeting the needs of proactively preparing frontline healthcare workforce for future emergencies, we have obtained permission from the John Hopkins Press (19) and the author ([name]) to: (A) translate the RAPID PFA guide into Chinese; (B) adapt this training into Chinese frontline context; and (C) evaluate this adapted Chinese PFA training intervention for frontline healthcare workers.

An appropriate adaption of a psycho-educational intervention is essential to maximize the implementation fidelity and enhance program fit (46). Given evidence on proper PFA adaptation resulting in PFA practice dilution (30), therefore, the adaptation of this Chinese PFA training intervention had been systematically conducted in line with these frameworks, i.e., the ADAPT-ITT cultural adaptation framework combined with the Bernal framework (47, 48). The aspects of language, metaphors, content, concept, goals, methods, and the context, as well as environmental and psychological factors had been well-considered when culturally adapting this training. Throughout this process, stakeholder participation in its development was achieved through: (A) conducting individual interviews (*n* = 15) of healthcare staff to capture their perceived needs (e.g., case range of application context) and training preferences; and (B) conducting three focus groups of frontline healthcare workers (with a total of 33 participants); and (C) using semi-structured discussions with an expert steering group to ensure cultural appropriateness. Drawing on the data collected from these stakeholders, we have identified possible adaptations and refined the PFA training intervention to fit Chinese healthcare practice. Thus, the “Preparing Me” PFA training intervention has been well-tailored to the Chinese frontline healthcare setting (see Table 1 of detailed PFA training intervention content based on TIDieR checklist) (49). Along with the consultation with experts in simulation and clinical education, this adapted Chinese PFA training program include a brief didactic introduction, role-play, case-simulation, and associated learning tools following an interactive and practice-based curriculum design (50–52). These will be delivered over 1-day face-to-face simulation training course (7 h) and two follow-up practice supervision sessions (1 h each); with a focus on improving the trainers' knowledge, skills, and self-efficacy related to support people in acute stress. All six modules comprise didactic information on mental health response to critical incidents and PFA, and each is framed by common challenges in frontline practice to increase its salience and provide practical approaches to implementing PFA into frontline healthcare practice. Training sessions are standardized via the use of a structured trainers' guide including up to 20 trainees. Since prior evidence on 1-day PFA training resulting in inconsistent PFA practice (30), we have added the two follow-up sessions to further support knowledge acquisition and skills development into their clinical practice.

**Table 1 T1:** “Preparing Me” for Chinese frontline healthcare PFA training intervention.

**Training session (length)**	**Description of element content**	**Learning objectives**	**Implementation of element**	**Supporting materials**
Session 1: Introduction (30 min) Trainer: Psychologist	• What is PFA? • Theoretical background of PFA: • terms and concepts of early psychosocial support in emergencies • Historical context of PFA and its application	• Increasing awareness of mental health crisis, the context of applying PFA knowledge and skills	Location: Classroom lecture Mechanism: Group discussion	Theoretical dialectic slides Training handbook
Session 2: Establishing rapport (75 min) Trainer: Psychologist	• Reflective listening • Establishing rapport with acutely distressed people	• Increasing reflective listening through a greater awareness of one's emotion. • Fostering the ability to be supportive of one's emotional needs • Approaching people with proper communication skills	Location: Classroom Lecture Mechanism: Cased-based simulation Guided debriefing Group reflection	Theoretical dialectic slides Training handbook Case highlights
Session 3: Assessment and periodization (75 min) Trainer: Psychologist	• Assessment people's needs through listening to their story • Help people to prioritize practical concerns	• Enhancing the ability of assessing and prioritizing people with obvious urgent basic needs	Location: Classroom Lecture Mechanism: Watch video Cased-based simulation Guided debriefing Group reflection	Fast checklist leaflet Training handbook Case highlights
Session 4: Intervention and Referral (75 min) Trainer: Psychologist	• Calm people via cognitive reframing, stress management, etc. • Instill hope and connect people with loved ones and social support • Encouragement with further resources • Follow-up	• Focusing on stress reduction • Improving emotional regulation and thus lowering stress levels known to have a negative impact • Supporting continued care with referral resources based on local circumstances	Location: Classroom Lecture Mechanism: Cased-based simulation Guided debriefing Group reflection	Fast checklist leaflet Training handbook Case highlights Referral resources
Session 5: Selfcare and wrap-up (75 min) Trainer: Psychologist	• Risk factors of being a supporter • Self-care strategy	• Promoting self-care and generate motivation for care for oneself	Location: Classroom Lecture Mechanism: Group discussion	Stress management resources
Supervision session 1 (45 min) Supervisor: Psychologist	• Reflect PFA practice within frontline context	• Reflect real-setting skill practice	Location: WeChat Cased-based learning Mechanism: Practice case counseling	Supervision Handbook Referral resources
Supervision session 2 (45 min) Supervisor: Psychologist	• Proper evaluate PFA delivery • Develop supporting and safety plan	• Review knowledge and skill acquisition	Location: WeChat Cased-based learning Mechanism: Practice case counseling	Supervision Handbook Referral resources

*The reporting of this training content has been mapped using TIDieR checklist including theory (why), material and procedures (what), training provider (who), mechanism of delivery and location (how and where), training schedule and intensity (when and how much), adaptation (tailoring), adherence and fidelity (how well)*.

Thus, as a prerequisite to conducting a main RCT to evaluate its effectiveness in a larger sample, this present study is designed with the overall aim to establish the feasibility of this Chinese PFA training intervention (“Preparing Me”) to inform future design and process. It is the second phase of an inter-linked project, with the interest in exploring the potential of a capacity building program in response to vulnerable frontline health workers combatting COVID-19. It is anticipated that the resulted information would be an impetus to maximize usability and acceptance of this low-intensity skillset by wider frontline population, thus achieving the empowerment of the frontline healthcare workforce in dealing with crises through which preparing them the ability to recognize and responding to psychological distress.

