#### (A) Feasibility Randomized Controlled Trial

A two-arm, feasibility randomized control trial will be used to test an adapted PFA training in a Chinese population of frontline healthcare workers. The purpose of the feasibility trial is to achieve two objectives (1) to determine the acceptability and feasibility of outcome data collection; and (2) to generate preliminary estimates of variability in trainee outcomes, which can inform sample size estimation for a large-scale RCT.

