### Intervention

#### Intervention

The whole process of this PFA training adaptation for delivery to Chinese frontline healthcare workers has been systematically described elsewhere. A detailed description of the Chinese ‘Preparing Me’ PFA training content has already been structured using the template for intervention description and replication checklist (TIDieR) in Table 1. Four trainers who have teaching and clinical psychological counseling background will be trained to deliver the PFA training intervention. Each of the six modules will be delivered in 75-min session blocks, incorporating didactic lectures, group exercises, role playing, and discussions to encourage active engagement and to improve the acquisition of PFA knowledge, skills, and techniques. All these sessions will be audio-recorded in preparation for the researchers to assess the fidelity using a PFA fidelity assessment tool. To support frontline healthcare participants to be able to apply the knowledge, skills, and techniques to their practice, two WeChat-based online supervision sessions will be offered.

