#### Psychoeducation Programme (Control)

Participants in the control arm will receive the best available alternative to PFA training, which in this setting is the hospital's existing 1 day psychoeducation training course. This involves a series of lectures on basic mental health training topics, including the traditional Chinese culture, understanding psychological crisis and skills, referral resources, and ethics.

This study will attempt to minimize contamination between the two arms through (A) engaging different trainers with equivalent clinical and training experience to deliver the training; and (B) consenting participants in both arms will be asked not to share information regarding the training that they have received with colleagues who might be involved in a different arm of the trial.

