### Statistical Data Analysis

Since this is a feasibility study and is not testing hypotheses regarding effectiveness of PFA training intervention, inferential statistics will not be employed. The primary objectives will be addressed via generating estimates of dispersion and central tendency (i.e., proportions, means, SDs, etc.). The acceptable levels of eligibility and enrolment will be a 90% or greater screening eligibility rate for frontline healthcare workers referred to the study. A recruitment rate is expected of 15 trainees per week and the target sample size would therefore be achieved in 6 weeks. The acceptable proportion of enrolled trainees who complete all the training sessions will be 80% or greater, given that there's 18% dropout rate of participants in PFA training cluster RCT (23). The feasibility of collecting quantitative outcome data includes (1) <20% missing data at the group level for each time point and (2) generating estimates of effect and variability related to by the independent research facilitator. Quantitative secondary objectives will be addressed via generating bivariate correlations and regression coefficients for the selected measures. Correlations between the baseline and follow-up will be estimated for continuous outcomes. Measures will be examined for multi-collinearity, as well as any needed transformation due to unfavorable skewness and kurtosis (72, 73). Appropriate 95% confidence intervals will be reported, with differences deemed significant at the 5% level.

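### PFA is taught in classes of up to 20, but the analysis and sample-size text allow for neither class nor trainer: intervals computed as for independent participants would be too narrow at any positive ICC

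*Protocol article*

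**What the plan says.** Allocation is individual and 1:1 (Protocol article, Randomization), with a target of 80, hence 40 per arm.

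Delivery is in groups. The section on the Preparing Me program describes sessions standardized by a trainers' "guide including up to 20 trainees". The Intervention section describes session blocks "incorporating didactic lectures, group exercises, role playing, and discussions to encourage active engagement", and Table 1 adds simulation, debriefing and group reflection. On staffing, the Intervention section says: "Four trainers who have teaching and clinical psychological counseling background will be trained to deliver the PFA training intervention". How trainers are assigned to classes is not stated.

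The control arm receives the hospital's existing "1 day psychoeducation training course. This involves a series of lectures on basic mental health training topics". To limit contamination, the plan relies partly on "engaging different trainers with equivalent clinical and training experience to deliver the training". The number and size of control classes are not given.

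Statistical Data Analysis lists means, SDs, correlations, regression coefficients and estimates of effect and variability. It then says "Appropriate 95% confidence intervals will be reported" and sets a 5% level for differences. Neither that section nor Sample Size mentions class, trainer or an ICC; the word cluster occurs only in describing the trial cited for its dropout rate.

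One stated purpose of the trial is "to generate preliminary estimates of variability in trainee outcomes, which can inform sample size estimation for a large-scale RCT".

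**The concern.** People taught together share a trainer, a room and the same discussions and debriefing, so their outcomes may be more alike than those of people in different classes. Individual randomization does not remove this, because the correlation arises after allocation. Using different trainers in each arm also means that trainer differences sit inside the comparison between arms.

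Two things are at stake. First, a between-arm interval or 5% test that treats the participants as independent understates the uncertainty. Second, this trial is meant to supply inputs for sizing a larger one. For an intervention taught in groups, the SD is only one of those inputs: class size and an ICC are needed too, and the plan names neither.

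**Working it through.** **The plan's own figure.** 64 completers with 20% loss gives 64 / (1 − 0.20) = 80, as stated. It rests on a feasibility rule of thumb, not on power, so clustering does not make it wrong.

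**Inputs.** n = 40 per arm (80 at 1:1). Class size m is at most 20, so at least 40 / 20 = 2 PFA classes. The ICC is not given; 0.01 to 0.10 is assumed. Control class size is not given, so two structures are shown.

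**Formulas.** Classes of m in both arms: design effect DE = 1 + (m − 1) × ICC. Only the PFA arm clustered: DE = (1 + [1 + (m − 1) × ICC]) / 2. The interval should be about √DE times its independent-participant width.

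| ICC | DE, m = 20, both arms | Width factor | DE, m = 20, PFA only | Width factor |
|---|---|---|---|---|
| 0.01 | 1.19 | 1.09 | 1.09 | 1.05 |
| 0.02 | 1.38 | 1.17 | 1.19 | 1.09 |
| 0.05 | 1.95 | 1.40 | 1.48 | 1.21 |
| 0.10 | 2.90 | 1.70 | 1.95 | 1.40 |

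Example at ICC 0.05: 1 + 19 × 0.05 = 1.95 and √1.95 = 1.40; with PFA only, (1 + 1.95) / 2 = 1.48 and the factor is 1.21.

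**Smaller classes.** With 16 per class (20 less 20% loss), the factor over the same ICC range is 1.07 to 1.58 for both arms and 1.04 to 1.32 for PFA only. With classes of 10 it is 1.04 to 1.38 and 1.02 to 1.20.

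**Coverage.** With classes of 20 in both arms, a nominal 95% interval computed as for independent participants covers about 93%, 91%, 84% and 75% at the four ICCs. A simulation with two classes of 16 completers per arm (20,000 runs, no true effect) gave 92%, 86% and 77% at ICC 0.02, 0.05 and 0.10.

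**The SD.** The expected within-arm variance, relative to the true one, is 1 − ICC × (m − 1) / (n − 1). At m = 20, n = 40 and ICC 0.10 this is 1 − 0.10 × 19 / 39 = 0.951, so the SD is 0.975 of its true value, or 2.5% low. At ICC 0.01 it is 0.2% low.

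**Why the ICC cannot be estimated here.** Two classes per arm leave 2 × 2 − 2 = 2 degrees of freedom between classes. An interval based on class means would use t = 4.30. At ICC 0.05 and m = 20, its half-width is 4.30 × √(2/40 × 1.95) = 1.34 SD, against 0.44 SD for the independent-participant interval.

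**Illustration for a main trial.** Assume a standardized difference of 0.5, 80% power and two-sided 5%; neither difference nor power is in the document. The independent calculation gives 63 per arm. With classes of 20 in both arms, 63 × DE rounds up to 75, 87, 123 and 183 per arm at ICC 0.01, 0.02, 0.05 and 0.10. Left at 63, power would be 73%, 67%, 52% and 38%.

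**The case against.** The strongest reply is that this rests on silence. The article nowhere says that independence is assumed, it gives no interval method, and its promise of appropriate intervals leaves room for an adjustment. A fuller plan may settle it. That stands, and it is why the claim about the intervals is conditional.

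The consequence within this trial is also limited. The aims are largely recruitment, retention, adherence and data completeness, and the Conclusions section ties progression to 80% retention, not to a between-arm interval. Statistical Data Analysis also disclaims inferential statistics before setting a 5% significance level. That contradiction needs its own resolution; if testing is dropped, the point about the 5% rule falls away and the point about the intervals remains.

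The size may also be smaller than the top of the range. Twenty is a maximum, four trainers are compatible with smaller classes, and the structured guide and fidelity ratings may reduce differences between trainers. With PFA classes of 10 and an unclustered control arm, ICC 0.05 widens the interval by only about 11%, and ICC 0.02 by about 4%.

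A reader might go further and infer that the SDs and effect estimates are wrong as well, or that the main trial will be under-sized. The document supports neither. Clustering alone leaves the effect estimate unbiased and barely moves the SD. No main-trial calculation is given; under-sizing would follow only if that calculation left out a design effect.

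**Conclusion.** The point holds in conditional form. Group teaching is explicit for PFA and a fair inference for a lecture course, and the analysis and sample-size text allow for neither class nor trainer. Between-arm intervals and 5% tests computed as for independent participants would be too narrow at any positive ICC. For an assumed ICC of 0.01 to 0.10, the shortfall is a factor of 1.09 to 1.70 with classes of 20 in both arms, 1.05 to 1.40 if only PFA is clustered, and less with smaller classes.

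The target of 80 is not at fault. What matters most is the hand-over to the main trial: an SD by itself is not a sufficient sizing input for a group-taught intervention. This is a worthwhile, inexpensive improvement and does not show that the trial is invalid.

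**What to change.** 1. Record class and trainer for every participant, and report the number and size of classes in both arms.
2. Show outcomes by class.
3. Describe individual-level intervals as conditional on the classes run. Beside them give a sensitivity interval widened by √(1 + (m − 1) × ICC) for ICC 0.01 to 0.10, with the partially nested version if the control arm is not clustered.
4. State that about two classes per arm cannot usefully estimate the ICC.
5. State that SD-based projections for the main trial will be shown multiplied by a design effect, using an ICC range from outside this trial.

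The cost is two identifier fields and a few lines of analysis and text. The downside is wider reported intervals and a larger projected main trial.
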